### Provisions for post-trial care {30}

The sponsor shall bear the cost of treatment and corresponding economic compensation for the subjects who suffer any damage or death related to the trial. The sponsor shall provide legal and economic guarantees to the researcher, except in the event of issues caused by medical malpractice.

### Outcomes {12}

#### Primary outcome

The histological assessment of gastric mucosal biopsies is the primary outcome of the study. OLGA and OLGIM staging will be used for pathological evaluation. The evaluation will be performed both before and after 24 weeks of administration of the treatment and any histopathological changes in the gastric mucosa will be compared between the two groups before and after 24 weeks of treatment. The outcomes will be divided into progressive, stable, and improved according to the OLGA/OLGIM stage after treatment. An increase in staging grade will represent progression, an unchanged staging grade will represent stability, and a reduction in staging grade will be considered an improvement.

#### Secondary outcomes

##### Endoscopic examination

Gastric atrophy before and after treatment will be assessed in terms of the Kimura-Takemoto classification.

##### Dyspepsia symptoms

A symptom score system will be used to evaluate the improvement in dyspepsia (Table 3). In the symptom score system, the score will be determined according to the severity, duration, and frequency of symptoms. The symptom scores will be recorded before administration and after 4 weeks, 12 weeks, and 24 weeks. The overall score represents the sum of all symptom scores. The dyspepsia symptom scores and the changes in each index value before and after treatment will be compared between groups. The treatment effect index (TEI) will be calculated as (pre-treatment integral − post-treatment integral)/pre-treatment integral × 100%. The curative effect classification is as follows: TEI ≥ 90% indicates clinically cured; 90% > TEI ≥ 70% indicates marked efficacy; 70% > TEI ≥ 30% indicates efficacy; TEI < 30% indicates invalid.

**Table 3 Tab3:** The symptom score system for chronic atrophic gastritis

Symptom	Score	Degree	Grading system
Epigastric pain	1	None	-
	2	Mild	< 2 times a week
	3	Moderate	≥ 3 times a week, not every day
	4	Severe	Every day, intermittently
	5	Extreme severe	Every day, almost continuously
Epigastric distention	1	None	-
	2	Mild	< 2 times a week
	3	Moderate	≥ 3 times a week, not every day
	4	Severe	Every day, intermittently
	5	Extreme severe	Every day, almost continuously
Epigastric discomfort	1	None	-
	2	Mild	< 2 times a week
	3	Moderate	≥ 3 times a week, not every day
	4	Severe	Every day, intermittently
	5	Extreme severe	Every day, almost continuously
Early satiety	1	None	-
	2	Mild	< 2 times a week
	3	Moderate	≥ 3 times a week, not every day
	4	Severe	Every day, intermittently
	5	Extreme severe	Every day, almost continuously
Heartburn	1	None	-
	2	Mild	< 2 times a week
	3	Moderate	≥ 3 times a week, not every day
	4	Severe	Every day, intermittently
	5	Extreme severe	Every day, almost continuously
Acid regurgitation	1	None	-
	2	Mild	< 2 times a week
	3	Moderate	≥ 3 times a week, not every day
	4	Severe	Every day, intermittently
	5	Extreme severe	Every day, almost continuously
Belching	1	None	-
	2	Mild	< 2 times a week
	3	Moderate	≥ 3 times a week, not every day
	4	Severe	Every day, intermittently
	5	Extreme severe	Every day, almost continuously
Abdominal discomfort	1	None	-
	2	Mild	< 2 times a week
	3	Moderate	≥ 3 times a week, not every day
	4	Severe	Every day, intermittently
	5	Extreme severe	Every day, almost continuously
Total symptom score	Equal to the sum of the above scores		

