Analysis of efficacy will be carried out in both FAS and PPS. According to the OLGA/OLGIM staging changes after treatment, the efficacy of CAG will be divided into progressive, stable, and improved. The numbers and percentages of cases will be calculated according to the efficacy rate. The CMH chi-square test stratified by center will be used to compare the two groups, and the 95% confidence interval of the rate difference between the two groups will be calculated. The curative effect on clinical symptoms will be calculated by the number and percentage of cases classified as cured, markedly effective, effective, and ineffective. The CMH chi-square test stratified by center will be used to compare the two groups. For the assessment of the changes in mucosal histology before and after treatment, changes after treatment will be evaluated relative to the baseline, and the number of cases, means, standard deviations, medians, maxima, and minima will be calculated and compared within the groups using paired *t*-test/signed-rank tests and compared between the two groups by analysis of variance. A covariance analysis model will be used to compare the difference between the two groups after treatment relative to the baseline. In the model, the baseline will be taken as the covariate, and the effects of grouping and center will be considered. The least-squares mean and 95% confidence interval of the difference between the groups are calculated based on this model.

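### The dyspepsia treatment effect index cannot exceed 80% on the 1-to-5 symptom scale, so the 'clinically cured' class (90% or more) is empty by construction

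*Protocol article*

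**What the plan says.** The scale, the index and the cut-offs are all fixed in the protocol article, Outcomes {12}, under Dyspepsia symptoms.

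- **Scale.** Table 3, titled "The symptom score system for chronic atrophic gastritis", lists eight symptoms. The lowest category is scored 1, as in the first row, "Epigastric pain 1 None". The highest is scored 5, "Every day, almost continuously".
- **Total.** The text says "The overall score represents the sum of all symptom scores", and the last row of Table 3 says "Equal to the sum of the above scores".
- **Index.** TEI is the pre-treatment score minus the post-treatment score, divided by the pre-treatment score, as a percentage.
- **Classes.** "TEI ≥ 90% indicates clinically cured; 90% > TEI ≥ 70% indicates marked efficacy". From 30% to below 70% is efficacy, and below 30% is invalid.

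Statistical methods {20a} then reports symptom efficacy as the "number and percentage of cases classified as cured, markedly effective, effective, and ineffective" and compares the arms with a CMH test stratified by center. Separately, Dyspepsia symptoms also plans a between-group comparison of the symptom scores and their changes.

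**The concern.** A percentage reduction has its usual meaning only if zero stands for no symptoms. Here the absence of all symptoms scores 8, and that floor stays in the numerator's post-treatment term and in the denominator. Full recovery therefore cannot give a 100% reduction, and cut-offs such as 90% and 70% do not mean what their labels say. At stake are a top class that nobody can enter, a class for full responders that reflects how ill they were at entry, and a published table reading 0% cured in both arms, which readers could take for a clinical result.

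**Working it through.** **Inputs** (all from Dyspepsia symptoms and Table 3): 8 items; item minimum 1; item maximum 5; total = plain sum; TEI = (pre − post)/pre × 100; cut-offs 90, 70 and 30.

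**Range of the total.** Minimum 8 × 1 = 8. Maximum 8 × 5 = 40.

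**Ceiling.** TEI is largest with the highest baseline and the lowest final score: (40 − 8)/40 = 32/40 = 80.0%. Enumerating every pair of totals from 8 to 40 finds none at 90% or above. If the formula were applied to a single item, the ceiling would be the same: (5 − 1)/5 = 80%.

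**Class of a complete responder (post = 8).** TEI = (pre − 8)/pre.

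- TEI ≥ 30% needs pre ≥ 8/0.7 = 11.4, so 12 or more.
- TEI ≥ 70% needs pre ≥ 8/0.3 = 26.7, so 27 or more.
- TEI ≥ 90% needs pre ≥ 8/0.1 = 80, twice the maximum of the scale.

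| Baseline total | TEI with all symptoms gone | Class |
|---|---|---|
| 9–11 | 11.1–27.3% | invalid |
| 12–26 | 33.3–69.2% | efficacy |
| 27–40 | 70.4–80.0% | marked efficacy |
| none | – | clinically cured |

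For example, a patient with all eight symptoms moderate (8 × 3 = 24) who recovers fully has 16/24 = 66.7%, 'efficacy'. A patient with one symptom scored 4 (total 7 + 4 = 11) who recovers fully has 3/11 = 27.3%, 'invalid'.

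**Order of patients.** 40→12 gives 28/40 = 70.0%, 'marked efficacy', with symptoms remaining. 26→8 gives 18/26 = 69.2%, 'efficacy', with none remaining. The partial responder ranks above the complete one.

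**No baseline symptoms.** With pre = 8, post cannot be lower, so TEI ≤ 0 and the patient counts as 'invalid'. The inclusion criteria set no minimum symptom score, so such patients can enter.

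**With the floor removed**, TEI = (pre − post)/(pre − 8):

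| Pre→post | TEI as written | Floor removed |
|---|---|---|
| 11→8 | 3/11 = 27.3%, invalid | 3/3 = 100%, cured |
| 14→9 | 5/14 = 35.7%, efficacy | 5/6 = 83.3%, marked |
| 20→8 | 12/20 = 60.0%, efficacy | 12/12 = 100%, cured |
| 26→8 | 18/26 = 69.2%, efficacy | 18/18 = 100%, cured |
| 40→12 | 28/40 = 70.0%, marked | 28/32 = 87.5%, marked |

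The index as written equals the floor-free index multiplied by (pre − 8)/pre. That factor is 3/11 = 0.27 at baseline 11 and 32/40 = 0.80 at baseline 40, which is why baseline drives the class.

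**The case against.** The arithmetic has no rescue: the ceiling is 80% for the total and for a single item, and nothing in the article rescores absent symptoms as 0 or subtracts the minimum. The case on the other side concerns reach, and most of it stands.

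- **The dyspepsia outcome as a whole.** A reader might infer that it fails. It does not. The abstract names the symptom score, not TEI or its classes, and changes and between-group differences in the score are the same when a constant is subtracted.
- **Direction of bias.** A reader might infer that the four-class test is pushed towards no difference. The documents do not allow that to be shown. An empty class is empty in both arms and drops out of the table, and the test remains valid under the null hypothesis. Lost sensitivity is plausible, because full responders are spread over lower classes, but its size depends on baseline scores that are not given.
- **Labels of recovered patients.** It would be too strong to say that they are all called 'efficacy' or 'invalid'. Those with a baseline of 27 or more reach 'marked efficacy'.
- **An existing remedy.** One might say that the plan already has a covariance analysis of the symptom total. In Statistical methods {20a} that model follows the sentence on mucosal histology and is not plainly assigned to symptoms. The method named there for symptom efficacy is the CMH test on the classes.

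**Conclusion.** Wrong as written, in a secondary outcome only. The 80% ceiling and the empty cured class are exact. They need no assumption about effect, variance or baseline, only the scale, sum, formula and cut-offs as printed. Full responders fall into three different classes according to baseline alone, and a partial responder can outrank a full one. The four-class table must therefore show 0% cured in both arms and may lose some sensitivity of unknown size. The primary histological outcome does not use TEI, the sample size section does not refer to it, and the planned comparison of raw scores and changes is intact. This is not a detail that could be left to a later analysis plan, because the protocol fixes all the elements and they contradict one another.

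**What to change.** Before unblinding, reconcile the scale with the cut-offs. Subtract 1 from each item (8 from the total) before computing the index, so that TEI = (pre − post)/(pre − 8) on the present scale, and keep the four cut-offs. Limit the TEI classes to patients whose recoded baseline is above 0, because the index is otherwise undefined, and report the number left out per arm.

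The cost is a wording change and one line of derivation code, with no new data. There is a downside to state: the index is coarse at very low recoded baselines. A patient with a recoded total of 1 can only have 100%, 0% or a negative value, and below a recoded baseline of 10 the 90% cut-off can be met only by complete resolution (10→1 is exactly 90%).

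Optionally, add a baseline-adjusted covariance analysis of the total symptom score as a supporting comparison. This should be written as a new specification. The error itself does not require it, nor does it require the TEI classes to become purely descriptive.

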#### Clinical manifestations and physical signs

Chronic gastritis has no specific clinical manifestations, such as epigastric pain, distention, belching, acid regurgitation, nausea, vomiting, and loss of appetite. The presence or absence of dyspepsia and its severity do not correlate significantly with the classification of chronic gastritis, its endoscopic features, or gastric mucosal histopathologic staging. Most patients have no obvious physical signs, although sometimes mild upper abdominal tenderness or discomfort may occur.

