#### Endoscopic and histopathological diagnosis

The endoscopic findings of chronic atrophic gastritis include mixed red and white coloration of the mucosa dominated by white mucosa, flat or even absent folding, exposure of part of the mucosal blood vessels, and a possible association with mucosal granules or nodules. The diagnosis of chronic atrophic gastritis includes both endoscopic and pathologic diagnoses, while atrophy diagnosed under white-light endoscopy has a low concordance with a pathologic diagnosis. The final diagnosis should be based on the pathologic diagnosis. The endoscopic gastric pattern is defined according to the Kimura-Takemoto classification (Table 1), based on the location of the endoscopic atrophic border (Fig. 3). The histopathological diagnosis refers to the pathological diagnostic criteria of chronic gastritis in China and the visual analog scale [13]. The severity of atrophic gastritis is defined according to OLGA and OLGIM [14, 15].

**Table 1 Tab1:** Kimura-Takemoto classification

Type	Classification	Definition
Closed Type	C-1	Atrophy visible in the antrum but not in the corpus
	C-2	Atrophy visible parabolically above the angulus and below the middle of the stomach on the lesser curvature
	C-3	Atrophy visible parabolically above the middle of the stomach on the lesser curvature
Opened Type	O-1	The atrophic border lies between the lesser curvature and the anterior wall
	O-2	The atrophic border lies on the anterior wall
	O-3	The atrophic border lies between the anterior wall and the greater curvature

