#### Inclusion criteria

Patients must meet the following criteria to be eligible for enrollment:Patients aged 18–70 years, male or femalePatients who meet the diagnostic criteria of chronic atrophic gastritis and who test negative for *Helicobacter pylori* (13C or 14C urea breath test is required)Patients with a pathological stage of OLGA-II/III. Two experts from the Department of Pathology will perform the diagnosis (pathological film reading), with consensus on the pathological conclusionPatients who have voluntarily agreed to participate and who have signed informed consent

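### Symptoms are not required at entry, yet the symptom response classes cover all efficacy patients, so a patient with no dyspepsia before or after treatment is counted as ineffective

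*Protocol article*

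**What the plan says.** **Entry.** The disease criterion is histological: "Patients with a pathological stage of OLGA-II/III". The other inclusion criteria are age, chronic atrophic gastritis with a negative breath test, and consent. Neither the inclusion nor the exclusion list mentions a symptom or a minimum symptom score. The diagnostic sections treat symptoms as incidental: "The presence or absence of dyspepsia and its severity do not correlate significantly with the classification of chronic gastritis" (Clinical manifestations and physical signs), and "The final diagnosis should be based on the pathologic diagnosis" (Endoscopic and histopathological diagnosis).

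**Score.** Table 3 (Dyspepsia symptoms) has eight symptoms, each scored 1 to 5. An absent symptom scores 1, as in the row "Epigastric pain 1 None". "The overall score represents the sum of all symptom scores".

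**Response classes.** TEI is defined as ("pre-treatment integral − post-treatment integral)/pre-treatment integral × 100"%). A TEI of 90% or more is clinically cured, 70% to below 90% is marked efficacy, and 30% to below 70% is efficacy. For the rest, "TEI < 30% indicates invalid".

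**Analysis.** "The curative effect on clinical symptoms will be calculated by the number and percentage of cases classified as cured, markedly effective, effective, and ineffective" (Statistical methods {20a}). The arms are compared by a CMH test stratified by center. Efficacy is analysed in the FAS, which is every randomised patient treated at least once, and in the PPS. Neither set depends on symptoms, and section {20b} plans no subgroup analyses.

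**The concern.** A response class based on percentage improvement only has meaning for someone who can improve. This trial selects patients on histology and says itself that dyspepsia may be absent, so patients without symptoms can be enrolled. They then enter the responder table as treatment failures, whichever arm they are in and whatever happens to them. The ineffective percentage would mix true non-response with having nothing to treat. The effective rates and their difference would depend on how many such patients happened to be recruited, which makes them hard to use for planning the phase III trial that the protocol has in view.

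**Working it through.** The protocol states no rate, power or count for the symptom outcome, so there is no figure of its own to reproduce.

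**1. Range of the total (Table 3).** Eight items scored 1 to 5 give a minimum of 8 × 1 = 8 (no symptom) and a maximum of 8 × 5 = 40.

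**2. The patient without symptoms.** TEI = (8 − 8)/8 = 0%, which is below 30%, so the class is invalid. If a symptom appears, the post-treatment total exceeds 8 and TEI is negative, which is also invalid. No other class is possible.

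**3. The same patient if an absent symptom scored 0.** TEI = (0 − 0)/0, which is undefined. The label invalid therefore comes from the 1-based coding combined with the absence of a symptom criterion. Recoding alone would replace a wrong class with no class.

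**4. Patients with symptoms that resolve fully (post-treatment total 8), on the current scale.**

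| Baseline total | TEI | Class |
|---|---|---|
| 9 | 1/9 = 11.1% | invalid |
| 10 | 2/10 = 20.0% | invalid |
| 11 | 3/11 = 27.3% | invalid |
| 12 to 26 | 33.3% to 69.2% | efficacy |
| 27 to 40 | 70.4% to 80.0% | marked efficacy |

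The largest possible TEI is (40 − 8)/40 = 80%, so nobody can be clinically cured. Removing the asymptomatic patients is therefore not enough on the current scale. With the total minus 8 in the formula, full resolution from any symptomatic baseline gives 100%.

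**5. Dilution.** Let a be the asymptomatic share, equal in expectation in both arms, and let p1 and p2 be the response rates among symptomatic patients. Counting everyone, the rates are p1(1 − a) and p2(1 − a), and the difference is (p1 − p2)(1 − a).

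**6. Illustration.** These inputs are assumptions, not protocol figures: p1 = 60%, p2 = 40%, two-sided α = 0.05. The 120 per arm is the planned 240 divided by 2. Power = Φ(d/SE − 1.96), with SE = √[r1(1 − r1)/n + r2(1 − r2)/n].

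- Counting everyone at a = 20%: rates 48% and 32%, d = 0.16, n = 120, SE = 0.0624, power = Φ(0.60) = 73%.
- Symptomatic patients only at a = 20%: rates 60% and 40%, d = 0.20, n = 96, SE = 0.0707, power = Φ(0.87) = 81%.

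| a | Difference, everyone | Power, everyone | Power, symptomatic only |
|---|---|---|---|
| 0% | 20 points | 89% | 89% |
| 10% | 18 points | 81% | 85% |
| 20% | 16 points | 73% | 81% |
| 40% | 12 points | 53% | 69% |

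A pooled-variance version gives values about 1 percentage point lower, with the same pattern. The right-hand column is an upper limit: it assumes that every retained patient can respond, and step 4 shows that this fails for totals 9 to 11 unless the score is rebased.

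**The case against.** - **This belongs to the SAP.** Who is evaluable for a secondary responder table is often settled there, and the SAP is not shown. It may restrict the denominator. But the article itself fixes the formula, the cut-offs, the analysis sets and the test, and followed as written they give the result above.
- **It is one readout of a secondary outcome.** This stands. The symptom scores and their changes are also compared between groups without the classes, so the symptom evidence does not rest on the responder table alone.
- **The size is assumed.** This also stands. The asymptomatic share and the 60% and 40% rates are not in the document, and no power is claimed for this outcome. At a = 10% the loss is about 4 points of power. A two-proportion test is also only a stand-in for the four-class CMH test.
- **A reader might infer a bias toward one arm, or treat a chance imbalance in asymptomatic patients as a spurious treatment effect.** The document supports neither. The dilution works in both arms and pulls the difference toward zero. Chance imbalance under randomisation is ordinary sampling variation that the test's error rate already covers. The planned baseline comparison, which includes single symptoms, would also show it.
- **A reader might infer that the entry criteria alone are to blame and the 1-to-5 coding plays no part.** Steps 2 to 4 show otherwise: the coding produces the label, and it also misclassifies patients who do have symptoms.

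**Conclusion.** The point holds as a minor-to-moderate defect of a secondary outcome. Two features act together: no symptom is needed to enter, and an absent symptom scores 1. As a result, a patient with nothing to treat is always counted as ineffective. That part is arithmetic from the protocol's own formula and needs no assumption.

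The size does need one. The responder rates and their difference shrink by (1 − a), and a is unknown; it could be close to zero or substantial. On the assumed rates with 120 per arm, the cost of counting everyone is up to about 4, 8 and 15 points of power at a = 10%, 20% and 40%. These figures illustrate the mechanism and do not estimate this trial's loss. The primary histological outcome is not affected, and nothing here indicates an advantage for either arm.

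**What to change.** In Dyspepsia symptoms and in Statistical methods {20a}:

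1. Apply the TEI classes only to patients with at least one symptom above 'None' at baseline. Table 5 schedules this score at the enrolment visit, before allocation, so the restriction respects randomisation.
2. Compute TEI on the total minus 8, so that no symptoms equals 0. Steps 1 and 2 are both needed: without the rebasing, full resolution from totals 9 to 11 stays invalid and clinically cured stays unreachable; without the restriction, TEI is undefined for asymptomatic patients.
3. Keep all patients in the between-group comparison of the total symptom score, adjusted for baseline and center. Name the symptom score explicitly, because the covariance model in {20a} follows a sentence about mucosal histology and is not clearly tied to symptoms.
4. List new symptoms in patients who were asymptomatic at entry, by arm.

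The cost is a few sentences of analysis wording, with no new data. The responder analysis will contain fewer patients, although those removed could not have responded. On the rebased score TEI is coarse at low baselines: from a rebased total of 1, a one-point fall is already 100%. The comparison of total scores should therefore be read alongside it.
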